Currently, meta-analyses have confirmed the positive impact of exercise interventions on the physical and psychosocial functioning and quality of life of transplant patients [15, 16]. However, as evidenced by the diversity of interventions and mixed hematologic and cancer populations, most of the existing studies have methodological limitations [17]. A mixed sample including both malignant and non-malignant hematology disorders that received HSCT was selected for most studies. No subgroup analysis was performed to determine whether it was the same hematologic disease. The symptoms and treatment modalities of patients with different hematologic diseases show significant differences. For example, malignant hematologic diseases (like leukemia) have a high risk of recurrence after transplantation, and disease recurrence is the leading cause of death after transplantation [18, 19]. By contrast, benign hematologic diseases such as AA have a lower risk of recurrence after transplantation, and the leading cause of death after transplantation refers to complications including graft-versus-host disease (GVHD) [20]. These differences in clinical characteristics support the need for exercise rehabilitation intervention studies in the HSCT-AA population. Meanwhile, we believe that studies on exercise interventions for malignant hematological diseases [21], lymphoma [22], and MDS [23] are also underway. To our knowledge, there is limited published literature on exercise rehabilitation in HSCT-AA patients. It provides an opportunity to examine the effectiveness of exercise interventions in benign but severe hematologic diseases such as HSCT-AA. The study hypotheses are as follows: (1) compared to the control group, exercise rehabilitation will result in a greater improvement on QoL (primary hypothesis); (2) compared to the control group, exercise rehabilitation will result in a greater improvement in muscle strength; (3) compared to the control group, exercise rehabilitation will result in greater improvement on fatigue and hematological indicators.

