### Sample size

PASS software was employed to assess the sample size. The sample size calculations were based on previous research on physical activity for hematopoietic stem cell transplantation for QoL [33]. The study will be a parallel-group randomized controlled trial with the quality of life being the primary outcome in the study. Based on a previous study [3], the mean QoL in the control group was estimated to be 56.3 ± 17.6, and exercise rehabilitation increased the QoL in the intervention group by 12.3 relative to the control group. With an alpha risk of 0.05 (bilateral) and a beta risk of 0.20, the sample size of each group was calculated to be at least 33 people. Considering the existence of factors including shedding, the samples were expanded by 20% on the premise of guaranteeing the minimum sample size. The samples were expanded to 41 cases in each of the two groups, with a total of 82 cases.

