## Statistical analysis

SPSS26.0 was adopted for statistical analysis of data. Missing data were filled in using the Last observation carried forward (LOCF) and statistical analysis was conducted following the intention-to-treat (ITT) principle. Statistical tests were carried out with two-sided tests and *P* 0.05 was considered a statistically significant difference. Gender, education level, marital status, exercise adherence, and incidence of adverse events were described as frequencies and percentages. In the meantime, age, duration of AA, time to HSCT and QoL, muscle strength, fatigue, PLT, Neu, HB, and Ret counts were described as means and standard deviations if they conformed to normal distribution, or median if they conformed to non-normal distribution. The chi-square test or *t-*test was employed to compare differences between the intervention and control groups. Taking into account the potential variations in age, gender, and education level, analysis of variance (ANOVA) was conducted to assess the development of outcomes over time. Additionally, repeated measures analysis was used to analyze scores at baseline and follow-up scores of all measures.

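### The quality-of-life analysis never uses the T0 score as a covariate, which forgoes power that the trial could have from data it already plans to collect

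*Protocol article*

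**What the plan says.** The Statistical analysis section names three methods for comparing the groups.

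- A chi-square test or t-test between groups, with no time point attached.
- An analysis of variance over time: "Taking into account the potential variations in age, gender, and education level, analysis of variance (ANOVA) was conducted". These three variables are the only ones named for adjustment.
- A further analysis: "repeated measures analysis was used to analyze scores at baseline and follow-up scores of all measures". T0 therefore stands beside the follow-up scores as something to be analysed. The section does not say whether the treatment effect is the group main effect, the group-by-time interaction or a contrast at one visit.

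Randomization and blinding says that participants learn their group only once the baseline assessments are done, so T0 is a pre-intervention measure. The Background words the primary hypothesis as a greater improvement in QoL.

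The Sample size section rests on a comparison of two means, with a control mean of 56.3, an SD of 17.6 and this assumed effect: "exercise rehabilitation increased the QoL in the intervention group by 12.3 relative to the control group". It ties the 12.3 to no visit and gives no correlation between baseline and follow-up.

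**The concern.** A patient's own QoL score before the intervention is a natural covariate for the later score, and the plan intends to collect it. A t-test at follow-up leaves the part of the variance that T0 explains in the error term. It also leaves any chance difference at T0 in the estimate. If the SD at T0 is also 17.6, the standard error of the T0 difference between groups is 17.6 × √(2/33) = 4.3 points at 33 per group, or 17.6 × √(2/41) = 3.9 at 41. With r = 0.5, a 4.3-point imbalance would carry about 0.5 × 4.3 = 2.2 points into an unadjusted T3 difference.

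Treating T0 as one of the repeated outcomes does not by itself solve this. The result depends on which term of the model is tested, and the section leaves that open. At stake is precision on the primary outcome in a trial of 82 patients.

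**Working it through.** **Inputs (Sample size section).** Difference 12.3; SD 17.6; "With an alpha risk of 0.05 (bilateral) and a beta risk of 0.20", so 80% power; 33 per group before the dropout allowance and 41 per group randomised. The plan specifies intention to treat with last observation carried forward, so up to 41 per group may be analysed. Both sizes are shown.

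**Assumptions.** r, the correlation between T0 and the follow-up score, is not in the documents and is taken as 0.3 to 0.7. The SD is 17.6 at every visit. The 12.3 is taken to be the T3 difference. For the repeated measures calculations, all pairs of visits have correlation r.

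**The plan's own figure.** n = 2 × (1.960 + 0.842)² × (17.6/12.3)² = 32.1, rounded up to 33, which agrees with "the sample size of each group was calculated to be at least 33 people". The t-test noncentrality is 12.3 / (17.6 × √(2/33)) = 2.84, giving 79.8% power (noncentral t). At 41 per group it is 3.16, giving 87.8%. The design is thus that of an unadjusted comparison at one time point.

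**T3 adjusted for T0, and T0-to-T3 change score.** The residual SD with adjustment is 17.6 × √(1 − r²), with one degree of freedom fewer. The SD of the change score is 17.6 × √(2(1 − r)). Power by noncentral t:

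| r | SD adjusted | power, 33 | power, 41 | SD change | power, 33 | power, 41 |
|---|---|---|---|---|---|---|
| 0.3 | 16.8 | 83.4% | 90.6% | 20.8 | 65.7% | 75.2% |
| 0.4 | 16.1 | 86.2% | 92.7% | 19.3 | 72.3% | 81.4% |
| 0.5 | 15.2 | 89.8% | 95.0% | 17.6 | 79.8% | 87.8% |
| 0.6 | 14.1 | 93.8% | 97.4% | 15.7 | 87.8% | 93.8% |
| 0.7 | 12.6 | 97.5% | 99.2% | 13.6 | 95.0% | 98.1% |

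Against the t-test, adjustment gains about 4, 6, 10, 14 and 18 points at 33 per group, and about 3, 5, 7, 10 and 11 at 41. It beats the change score at every r shown. The change score falls below the t-test when r is under 0.5 and exceeds it when r is over 0.5.

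**Repeated measures with T0 among the outcomes, 33 per group, effect of 12.3 at each of T1-T3.**

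- *Group main effect over T0-T3.* The expected difference at T0 is zero, so the average effect is 12.3 × 3/4 = 9.2. The SD of a four-visit mean is 17.6 × √((1 + 3r)/4). Power is 86%, 76% and 66% at r = 0.3, 0.5 and 0.7.
- *Group-by-time interaction (3 degrees of freedom).* The effect is not averaged down. Power is 68%, 84% and 97% at the same r.
- *T0-adjusted analysis of the T1-T3 mean, for comparison.* Power is 99%, 99% and above 99%.

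**The case against.** A reader might infer that the plan dilutes the treatment effect by averaging it over a visit where none can exist. The documents do not support this. Averaging down happens only if the group main effect over T0-T3 is the test, and the section does not say so. The hypothesis of greater improvement, and the stated interest in how outcomes develop over time, point rather to group by time or to change from T0. Neither of those is diluted, and both take account of a T0 imbalance, though less efficiently than a covariate does. Even the main effect is not always weak: at r = 0.3 and a constant effect it has 86% power, above the t-test and above the T3 adjusted analysis. Keeping T0 as an outcome is also no error if the two T0 means are constrained to be equal, but the section describes no such constraint.

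A reader might also take the loss to be about 10 points. That is a single cell, r = 0.5 at 33 per group. T0 is at engraftment, roughly day 14 (Adherence section), and T3 is at day 100, so r could be low; at r = 0.2 the gain at 33 per group is under 2 points (81.4% against 79.8%).

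Finally, this is a condensed article, and a separate analysis plan may define the contrast. That weakens any complaint about what is left unsaid. It does not answer what is said: the article lists its adjustment variables without the T0 score, and it assigns T0 the role of an analysed score.

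**Conclusion.** The point holds as forgone efficiency. As written, no named analysis adjusts for the T0 score. For a T3 difference of 12.3 with SD 17.6, adjustment would raise power from 80% to 83-97% at 33 per group, and from 88% to 91-99% at 41 per group, for r between 0.3 and 0.7. The size rests on that assumed r, on a common SD and on reading the 12.3 as a T3 difference.

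Randomisation keeps the unadjusted comparison unbiased, and the stated 33 per group still delivers about 80% power without adjustment. Power clearly under 80% arises only under particular combinations of tested term, correlation and number analysed, and the documents fix none of these combinations. The change is worth making because adjustment does better than both the t-test and the change score throughout the range examined, and needs no extra patients or visits.

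**What to change.** Replace the three overlapping methods for primary QoL with one model: T1, T2 and T3 scores as outcomes, the T0 score as covariate, and group, visit and group by visit as terms. Age, gender and education level can stay if wanted. Name the group difference at T3 as the primary contrast. An equivalent choice is to keep T0 as an outcome and constrain the two group means at T0 to be equal. Use the same model for the other repeated continuous outcomes: grip strength, sit-to-stand time, fatigue and blood counts.

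Reconcile the assessment schedule at the same time. Table 1 marks the QLQ-C30 at t1 to t3 but not at t0, while the Abstract, Trials design, and Primary and secondary outcomes sections say that all outcomes are measured at T0. Without that score the adjustment cannot be made.

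The cost is a change of analysis wording. The one downside is that the covariate version needs a simple prespecified rule for patients without a T0 score, such as imputing the mean.

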## Ethical considerations

The study was approved by the Ethics Committee of The First Affiliated Hospital of Zhejiang Chinese Medical University (Zhejiang Provincial Hospital of Chinese Medicine) (Ethical approval ID: 2022-KL-095-01). All participants were informed of the purpose, requirements, procedure, and study methods of the study prior to signing the written informed consent. Participants could withdraw from the study at any time without affecting their treatment. Personal data collected during the study will be kept strictly confidential and used only for this specific research project, not for any other purposes.

## Discussion

This study was aimed at evaluating the effectiveness of exercise rehabilitation in HSCT-AA patients from a Chinese single center. Currently, there is no standardized, widely accepted, and referenced exercise intervention for HSCT-AA patients, and it is particularly important to conduct such studies for this population.

The results of this study help provide scientific and practical knowledge to support the rehabilitation of HSCT-AA patients and improve their QoL. Expectedly, this study is acceptable and feasible as an important step in the field of exercise rehabilitation in benign hematological treatment and may provide useful information for health care.

### Limitations

Several limitations should be noted in this work. Firstly, HSCT-AA patients may be frail due to treatment and disease, and the patient attrition may be high after follow-up for 100 days post-transplantation. We will consider other measures to remind patients to participate in the follow-up study. Secondly, the control group was mainly provided with usual care together with exercise-related health education, which may have underestimated the intervention effect. Nevertheless, we consider that it would be unethical to include control subjects without any intervention. Finally, the white paper report mentions that HSCT patients should receive multimodal interventions, including exercise, nutrition, and return to work [34]. However, this study did not include a nutritional assessment or dietary intervention, which is considered another limitation of this exercise-focused intervention.

## Conclusions

To conclude, this study will evaluate the effectiveness of exercise rehabilitation for HSCT-AA patients. If the intervention proves to be effective, it could be used on a large scale and widely in this population, which may enhance the quality of life of patients. Moreover, the evidence obtained from this study will provide evidence for future research and clinical practice.

## Trial status

The current protocol is version 1 of May 2022. Recruitment for this study begins in February 2023. The trial status is currently in the recruitment phase. Recruitment and trial are expected to be completed by August 2024.

## Data Availability

The datasets used and/or analyzed during the current study are available from the corresponding author on reasonable request.

## Abbreviations

AA: Aplastic anemia
HSCT: Hematopoietic stem cell transplantation
GVHD: Graft-versus-host disease
QoL: Quality of life
APBMT: Asia Pacific Blood and Marrow Transplantation
CBMTR: Chinese Blood and Marrow Transplantation Registry
AML: Acute myeloid leukemia
ALL: Acute lymphoblastic leukemia
MET: Metabolic equivalents
HHS: Health and Human Services
THR: Target heart rate
RPE: Rating of Perceived Exertion
EORTC QLQ-C30: European Organization for Research and Treatment of Cancer Quality of Life Questionnaire-Core 30
FTSST: Five Times Sit to Stand Test
BFI: Brief Fatigue Inventory
RBC: Red blood cell
PLT: Platelet
Neu: Eutrophil
HB: Hemoglobin
Ret: Reticulocyte
